## Abstract

**Introduction:**

Adults with cerebral palsy (CP) are at increased risk of non-communicable diseases and often experience secondary complications as they age. Physical activity can mitigate these risks and improve well-being. However, adults with CP face significant challenges in accessing structured, tailored exercise programmes due to limited service availability and environmental barriers. A group online exercise programme may overcome some of the barriers to accessing exercise faced by adults with CP. CP-EXCEL aims to evaluate the feasibility of an online exercise programme for adults with CP. The study will examine the demand, implementation, practicality, adaptability, acceptability, and potential efficacy of delivering the online exercise programme to adults with CP in Ireland.

**Methods:**

This feasibility randomised controlled trial will recruit 60 adults with CP. Participants will be randomly assigned to either an eight-week online exercise intervention or a control group. The feasibility of the programme will be evaluated across five key domains: 1) demand as indicated by recruitment rate; 2) implementation as indicated by attendance; 3) practicality as indicated by number and type of adverse events; 4) adaptability, by examining how the programme accommodates varying levels of mobility and associated impairments; and 5) acceptability explored through semi-structured interviews with participants. To assess preliminary efficacy, the Patient-Reported Outcomes Measurement Information System (PROMIS) will be used to measure changes in physical, mental, and social functioning at baseline and post-intervention. Quantitative outcomes will be analysed using linear mixed models, and qualitative data will be analysed using framework analysis.

**Conclusion:**

This study will provide valuable insights into the feasibility of an online exercise programme tailored for adults with CP And inform the design of a future fully powered randomised controlled trial.

## Background

Cerebral palsy (CP) is a lifelong neurological condition characterised by impaired movement, often in combination with cognitive, speech and sensory impairments.
^1^ In comparison to those without CP, adults with CP are less physically active and at higher risk of developing non-communicable diseases.
^2^
^,^
^3^ Further, many adults with CP experience pain, fatigue, decline in walking ability, reduced muscle flexibility and strength, and increased risk of falls with age.
^4^
^–^
^6^ These complications may restrict their capacity to engage in daily activities and lead to a diminished sense of participation.
^7^

Participation in exercise may reduce the risk of developing non-communicable disease and manage complications associated with CP and ageing.
^7^
^,^
^8^ Existing evidence suggests that individuals with CP can safely participate in structured exercise programmes incorporating aerobic and resistance training, typically performed 2–4 times per week.
^7^ Resistance training commonly involves 2–4 sets of 6–15 repetitions, with intensity and progression tailored to individual ability.
^7^ Emerging evidence also suggests that higher-intensity or power-based training may provide additional benefits for muscle strength and functional mobility in children and youth with CP.
^9^
^–^
^11^ The suitability of these approaches may vary depending on factors such as age, mobility level, safety considerations, and the ability to deliver such training within group-based or remote settings. However, adults with CP face challenges trying to access exercise programmes in the community, including lack of appropriate gym equipment, lack of transport, and inaccessible facilities.
^12^ Further, people with CP want support from physiotherapists with knowledge of CP who can adapt the exercises to suit their ability and provide advice on how to manage the complications of CP.
^12^
^,^
^13^ However, a recent study highlighted that 23% of adults with CP in Ireland have an unmet need for physiotherapy.
^14^ The most common reasons adults with CP accessed physiotherapy were for mobility decline, stiffness and pain.
^15^

In addition to physiotherapy-led interventions, evidence suggests that adults with CP have limited knowledge and support to effectively manage their condition and associated secondary complications.
^16^ Many report seeking information from the internet or peers rather than from health professionals.
^16^ Educational approaches can provide information on secondary complications associated with ageing in CP, which may support individuals to better understand and manage these challenges. Such approaches may complement exercise-based interventions by promoting self-management and supporting ongoing engagement in physical activity.

The increased use of online healthcare delivery since Covid-19
^17^ provides an opportunity to address some of the barriers that individuals with CP face in accessing physiotherapy-led exercise programmes. Online programmes may also have benefits over in-person programmes for people with CP such as increased opportunity for peer support and access to specialist knowledge regardless of geography, and enhanced comfort in their own home.
^18^ These group-based formats may also support social participation and mental wellbeing, which are closely linked to quality of life outcomes.
^19^
^,^
^20^

Recognising these challenges and opportunities, the CP-EXCEL study aims to evaluate the feasibility of an online exercise programme for adults with CP. CP-EXCEL refers to the feasibility randomised controlled trial designed to assess the delivery, acceptability and preliminary outcomes of this intervention. Findings from this study will inform the design and conduct of a future fully powered randomised controlled trial. If results indicate the programme is feasible, it may provide a sustainable approach to addressing the unmet need for physiotherapy among adults with CP and improve their health and participation.

### Aim

In this project, we will evaluate the feasibility of an online group-based exercise and education programme for adults with CP, compared to an education component. Six domains of an evidence-based framework for feasibility studies will be evaluated: demand, implementation, practicality, potential efficacy testing, adaptability and acceptability.
^21^

### Objectives are to

•Describe recruitment rate.•Describe fidelity to the programme.•Assess number and type of adverse events.•Explore acceptability and adaptability of the online exercise programme to adults with CP.•Investigate effects of the programme on physical, mental and social outcomes to inform the design of a future fully powered randomised controlled trial.

## Methods

### Study design

This is a feasibility randomised controlled trial designed to assess the feasibility of study procedures, including recruitment, randomisation, retention, intervention delivery, and outcome assessment, rather than to evaluate intervention effectiveness. Participants will be randomised to either an 8-week online exercise programme or a control group. Outcome measures will be collected at baseline and immediately post-intervention. The study is not powered to detect statistically significant differences in outcomes, and any analysis of outcomes will be exploratory in nature. This protocol is registered on
clinicaltrials.gov (
NCT06983782) available at [
https://clinicaltrials.gov/study/NCT06983782], registered 20
^th^ May 2025, last updated on 20
^th^ June 2025. The protocol is guided by the Standard Protocol Items: Recommendations for Interventional Trials (SPIRIT) guidelines (Appendix 1) Extended data.
^22^

### Participants

Participants will be recruited through newsletters and social media of organisations that offer services and support to adults with CP in the community across the island of Ireland, including the Central Remedial Clinic (CRC), Irish Wheelchair Association (IWA) and Mae Murray Foundation.

Sixty adults with CP will be recruited in total, with thirty participants allocated to the intervention group and thirty to the control group. This sample size is appropriate for a feasibility randomised controlled trial and is not based on a formal power calculation. It is informed by the study aim to assess feasibility parameters and by estimated recruitment rates of 5–10% from previous studies involving adults with CP in Ireland.
^14^

We will include adults aged 18 and over with CP residing on the island of Ireland in any Gross Motor Function Classification System (GMFCS) level.
^23^ Individuals with severe intellectual disability will be excluded where sufficient adaptations cannot be made to support them to access the online platform and follow study instructions. We will also exclude Adults with unstable medical conditions (e.g. heart conditions).

Participants will be supported to engage in the study using accessible materials and flexible communication approaches (e.g., simplified information or verbal explanation), and may be assisted by a family member or support person where appropriate (e.g., to support consent or participation in online sessions).

### Recruitment

The study procedure is outlined in
Figure 1. If interested in taking part, adults can contact the post-doctoral research fellow who will introduce the study, provide a participant information leaflet (PIL), and answer any questions. The PIL includes detailed information about the study, eligibility criteria, the consent and withdrawal processes, confidentiality, data protection, data storage, and the researchers’ contact details.

**Figure 1. f1:**
[figure not shown]
CP-Excel study design.

All participants will complete a brief screening survey which includes personal details (name, email/phone number), and any health concerns that may prevent them from safely engaging in the exercise programme. Medical stability will be assessed through self-report in this survey, including information on current health conditions and any contraindications to exercise, and clarified through follow-up discussion with the research team where required. The ability to participate in the study will also be assessed during screening and initial interaction with the researcher, considering communication, cognitive ability, and ability to follow instructions. Where appropriate, the potential for support from a family member or caregiver and the feasibility of making adaptations will be considered to facilitate participation. After the screening process, participants who meet the eligibility criteria will be asked to provide informed written or electronic consent to the post-doctoral research fellow.

Following screening and consent, all participants will undergo a baseline assessment via an online survey. Participants will be randomised to the intervention or control group, and then re-assessed at the end of week 8.

### Randomisation

Following the baseline assessment, participants will be randomly allocated to either an intervention or control group in a 1:1 ratio. Stratification will be based on their mobility status: GMFCS Level I-III (with or without walking aids) and GMFCS Levels IV-V (who use wheelchairs). The random allocation will be generated by a computer in random permuted blocks of 2 or 4, and implemented automatically within REDCap (Research Electronic Data Capture). Allocation concealment will be ensured as the sequence is embedded within REDCap and not accessible to the research team prior to assignment.

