The programme will be delivered by a physiotherapist (post-doctoral research fellow) and a specialist personal trainer in exercise for long-term neurological conditions. The programme content was developed with input from physiotherapists and personal trainers with expertise in CP, and from the Public and Patient Involvement (PPI) contributors who are adults with CP. The exercise programme will be piloted with PPI contributors in advance of the intervention commencing: any necessary refinements will be made based on feedback received. This will include refinement of adaptations to support delivery across a range of abilities and needs. During the intervention, adaptations will be informed by participant feedback and session experience. All adaptations made during programme delivery (e.g., modifications to exercises, level of support, or delivery approach) will be documented prospectively by the researcher delivering the intervention. The researcher delivering the programme will review sessions, document adaptations and implement any necessary adaptations in subsequent group classes. These documented adaptations will inform ongoing refinement of the intervention, interpretation of feasibility outcomes, and future implementation.

Detailed intervention materials, including exercise and educational content, will be made available alongside the publication of the study findings, informed by the feasibility outcomes.

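### Published blocks of 2 or 4 within two visible strata mean that hiding the list in REDCap does not by itself ensure concealment, because the fellow who recruits also delivers the classes

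*Protocol article*

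**What the plan says.** Under Randomisation, the protocol article states that "participants will be randomly allocated to either an intervention or control group in a 1:1 ratio", stratified by "GMFCS Level I-III (with or without walking aids) and GMFCS Levels IV-V (who use wheelchairs"), with the sequence "generated by a computer in random permuted blocks of 2 or 4". It then says: "Allocation concealment will be ensured as the sequence is embedded within REDCap and not accessible to the research team prior to assignment". Participants gives the total as 60, with 30 per arm.

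Roles are set out elsewhere. Under Recruitment, "adults can contact the post-doctoral research fellow who will introduce the study, provide a participant information leaflet (PIL), and answer any questions". The text after Figure 1 has the same fellow receive consent and adds that "The ability to participate in the study will also be assessed during screening and initial interaction with the researcher", weighing communication, cognition and whether adaptations are feasible. Under Intervention group, "The programme will be delivered by a physiotherapist (post-doctoral research fellow"), together with a specialist personal trainer. The order of events is screening, consent, baseline survey, randomisation. No blinding is described.

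**The concern.** Keeping the sequence in REDCap stops anyone reading the next entry. It does not stop someone inferring it from earlier entries, and very short blocks make that inference easy. The conditions for it are in the document:

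- The block sizes are published.
- The stratum is broadly visible, since it separates people who walk from people who use wheelchairs.
- One fellow recruits, takes consent and teaches the classes, and so knows who is in the intervention arm.
- Entry involves judgement.

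A recruiter who could foresee the next allocation might, without intending to, be swayed on a borderline eligibility decision, on encouragement, or on the timing of entry.

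Two things are at stake. The between-group estimates of the PROMIS outcomes are meant to inform the design and sample size of the next trial (Objectives, Discussion). And Study design lists randomisation among the procedures whose feasibility is being assessed, so a predictable scheme could be carried forward as one shown to work.

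**Working it through.** The protocol gives no predictability figure, so there is nothing of its own to reproduce.

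**Inputs from the document.** 1:1 allocation, two strata, blocks of 2 or 4, 60 participants.

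**Assumptions (not in the document).** Each block is of size 2 with probability q, taken as 1/2 and then varied. The strata hold 45 and 15 people. The observer knows the set of block sizes but not where blocks begin.

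**Step 1: second person in a stratum.** If the block has size 2, the second allocation is certainly the opposite arm. If it has size 4, it is the opposite arm with probability 2/3. So P(opposite) = q + (1 − q) × 2/3.
- q = 1/2: 0.5 + 0.5 × 2/3 = 0.833.
- q = 1/3: 0.333 + 0.667 × 2/3 = 0.778, which is below 80%.

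**Step 2: long-run share at 80% or more, q = 1/2.** The next allocation is informative whenever the stratum is unbalanced. A block of 2 has one such position. A block of 4 has two in 4 of its 6 orderings and three in the other 2, a mean of 7/3. The mean block length is 3. Share = (0.5 × 1 + 0.5 × 7/3) / 3 = 1.667 / 3 = 56%. Direct calculation at finite size gives 55% for a stratum of 30, 54% for 45 and 52% for 15. For strata of 45 and 15 that is 0.54 × 45 + 0.52 × 15 = about 32 of 60.

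**Step 3: full certainty.** This occurs when a block of 4 opens with two of the same arm (probability 1/3), which fixes the next two.
- q = 1/2: (0.5 × 1/3 × 2) / 3 = 11% in the long run; about 10% at these sizes.
- q = 1/3: mean block length 10/3, so (0.667 × 1/3 × 2) / 3.333 = 13%.

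**Step 4: other mixes.** With one third of blocks of size 2, the share at 80% or more is about 47% in a stratum of 30 or 45 (42% in one of 15). With one quarter it is 41% in a stratum of 30. At both mixes, in a stratum of 30, 56-57% are still predictable at 75% or more.

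**Step 5: people pending.** Suppose one person in the stratum has been screened but not yet randomised when the next is judged. With one allocation known at the start of a block, the chance that the next-but-one is the opposite arm is 0.5 × 0.5 + 0.5 × 2/3 = 0.583, no longer a confident prediction. Simulation gives the shares predictable at 80% or more (stratum of 45 / stratum of 15, equal mix, sizes known):

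| Pending in stratum | Blocks 2, 4 | Blocks 4, 6 | Blocks 4, 6, 8 |
|---|---|---|---|
| none | 54% / 52% | 28% / 30% | 23% / 19% |
| one | 5% / 5% | 12% / 11% | 13% / 11% |
| two | 0% / 0% | 1% / 1% | 2% / 2% |

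With none pending, fully certain predictions are about 10%, 6% and 2.5% for the three schemes, and best-guess success is 71-72%, 68-69% and 66-67%.

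**Step 6: imbalance (20,000 simulated trials, strata of 45 and 15).** The mean absolute difference between arms is 1.0 with blocks of 2 and 4 and 1.2 with 4, 6 and 8. The 95th percentile is 2 in every case. The largest difference seen with the longer blocks is 6 of 60.

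**The case against.** The strongest objection is about timing. Eligibility is judged at screening, but allocation follows consent and a baseline survey that, under Assessments, may be completed online, by phone, in person or on paper returned by post. The order of randomisation need not follow the order of screening. One person pending cuts the headline share about tenfold, and longer blocks are then more predictable than short ones if their sizes are known (11-13% against 5%). Sixty recruits in three months, if the period used in the Demand section is taken as the recruitment window, would be about 4 to 5 a week, so overlapping candidates are plausible. This stands, and it makes the size of the risk conditional. It does not remove the risk: candidates may enter one at a time, particularly in a small stratum, and the fellow may be able to influence when randomisation happens. The point about longer blocks is met by withholding their sizes.

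It is also fair that the average guess rate differs by only 3 to 5 percentage points between schemes, that outcomes are exploratory, that varying blocks held in REDCap are a recognised method, and that the document gives no motive for steering allocation. Short blocks also protect balance in a small stratum.

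A reader might infer that more than half of allocations are predictable as a matter of fact, or that the demand results (recruitment, reasons for exclusion) will be biased. The document supports neither. The first needs an equal mix of block sizes and nobody pending, and neither is stated. The second is speculation.

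**Conclusion.** The concern holds in a limited form. The list is concealed, but the statement that this ensures concealment claims too much, given published blocks of 2 or 4, two visible strata and one fellow who recruits and delivers.

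The size runs from about 52-54% of allocations predictable with at least 80% certainty (equal mix, all earlier allocations in the stratum known), through about 47% if one third of blocks have size 2, to about 5% with one person pending and none with two. The risk is greatest when candidates enter singly or when the timing of randomisation can be influenced.

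This rests on assumptions: the mix of sizes, the stratum split and the number pending are not given, and that the trial is open is inferred from the absence of any described blinding and from who delivers the classes. What is exposed is the exploratory between-group comparison and the case for reusing the procedure in the full trial. Nothing here suggests that anyone has steered or intends to steer allocation.

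**What to change.** For participants not yet randomised:

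- Rebuild the REDCap allocation table with larger, randomly varying blocks within each stratum, for example 4 and 6, or 4, 6 and 8.
- Have it built by someone who neither recruits nor delivers classes, and keep the new sizes from staff who do. Lengthening the blocks without withholding the sizes would not help when candidates overlap. The sizes already published no longer apply once the table is replaced.
- In the protocol, state only that block sizes vary, and replace the claim that concealment is ensured with a statement that the list is hidden and that block sizes are not disclosed to recruiting staff.

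If some participants have already been randomised under the present scheme, report that as a limitation.

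The cost is a new table and a revised sentence or two, plus slightly more possible imbalance: a mean of 1.2 rather than 1.0 participants, usually 2 or fewer, and at most about 6 of 60 in simulation.

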^28^ Findings from the balance and functional assessments will be used to inform the individualisation of the exercise programme, including appropriate exercise selection, level of difficulty, and required adaptations, to ensure safe and appropriate participation.•Environmental assessment for safe space. This assessment will evaluate the participant’s environment for potential trip hazards, the availability of a safe exercise space, proper screen setup, adequate lighting, and the presence of support persons if needed. Additional considerations will include ensuring access to a supportive chair or other necessary equipment, and technical support for accessing the online platform if required. Participants will also be required to sign a safety checklist following the assessment. confirming that they had received and understood the safety recommendations discussed during the assessment regarding exercise space, equipment, support persons if required, exercise warning signs, and exercising within their individual ability level.•Where risks are identified, efforts will be made to adapt the environment and exercises to support safe participation. Participants will not be excluded solely based on environmental constraints where reasonable adaptations can be made; however, if safety cannot be ensured, participants will not proceed to the intervention component of the study.

## Intervention group: Online exercise and education programme

The intervention is an 8-week online exercise and education programme consisting of an online exercise class once per week, in accordance with exercise prescription guidelines for people with CP.
^7^ The programme will consist of eight weekly group sessions, each lasting 60 minutes. Each session will include (i) 5–8 minutes for warm-up, a 30 minute exercise programme, 5 minutes for cool-down, and (ii) 15–20 minutes of interactive learning focused on a topic of relevance to adults with CP.

The online exercise class will focus on mobility, strength and balance exercises for major muscle groups, based on the most common reasons that adults with CP seek physiotherapy.
^15^ Balance will be both explicitly targeted and integrated within functional exercises throughout the programme. Participants will complete up to 10–11 exercises in each class. In standing, balance will be challenged through functional tasks such as sit-to-stand, squats, side stepping, toe taps and exercises involving weight shifting or changes in base of support. The exercises may be completed in sitting or standing depending on the person’s ability. For participants exercising in sitting, balance will be addressed through trunk control and postural stability activities, such as unsupported sitting, reaching tasks, and dynamic upper limb movements performed within a safe and supported environment. The intervention will be tailored to individual ability, with exercises adapted based on mobility level (GMFCS I-V), upper limb function, associated impairments (e.g. communication, vision, or hearing) and risk assessment findings, while maintaining a consistent overall structure. Where required, participants may be supported by a family member or caregiver to assist with communication, technology use, or safe participation. Participants will complete between 2 and 4 sets of 6–15 repetitions of each exercise. Exercises will focus on functional, task-oriented movements targeting mobility, strength, and balance. The programme will emphasise controlled, submaximal effort and movement quality rather than maximal or high-velocity (power-based) training. Exercise intensity will be individualised and guided by participant ability, with participants encouraged to work at a moderate level that is challenging but safe.

Participants will also be encouraged to repeat the exercises independently twice per week between sessions. Participants will be provided with access to private exercise videos demonstrating the exercises performed during the online sessions to support independent completion. Adherence to the intervention will be recorded through attendance at online sessions and a brief self-reported survey capturing whether participants completed the prescribed exercises independently at least twice per week. The number of sets and repetitions performed during supervised sessions will also be recorded, with progression guided by participant ability over the 8-week programme. Progression will be achieved by modifying repetitions, sets, range of movement, level of support, and exercise complexity, rather than through one-repetition maximum testing. Examples of exercises include overhead reach, Table or box push-ups, Lateral arm raises, Knee up, hip back or wheelchair dip, side step or hip out, sit to stand, squat, knee straight/bend, heel raises and seated rowing as well as balance-focused activities such as weight-shifting and reaching tasks. For example, exercises such as squats may be performed in standing with or without support or adapted to seated alternatives (e.g., sit-to-stand or wheelchair-based upper body movements) to accommodate different mobility levels. Exercises will be demonstrated with options and progressions to enable participation within a group setting while accommodating individual differences. Verbal cueing and demonstration will be used to guide correct technique, pacing, and safe execution of movements during each session.

The 15–20 minute interactive learning component of each weekly online class will consist of educational materials on exercise, nutrition, mobility changes, fatigue, optimising bone health, pain management, mental health, sleep and physical activity maintenance (one topic per week). Educational materials and exercises will be delivered during the online class. The educational content is consistent across both study groups; however, in the intervention group it is delivered interactively during weekly sessions.

The programme will be delivered by a physiotherapist (post-doctoral research fellow) and a specialist personal trainer in exercise for long-term neurological conditions. The programme content was developed with input from physiotherapists and personal trainers with expertise in CP, and from the Public and Patient Involvement (PPI) contributors who are adults with CP. The exercise programme will be piloted with PPI contributors in advance of the intervention commencing: any necessary refinements will be made based on feedback received. This will include refinement of adaptations to support delivery across a range of abilities and needs. During the intervention, adaptations will be informed by participant feedback and session experience. All adaptations made during programme delivery (e.g., modifications to exercises, level of support, or delivery approach) will be documented prospectively by the researcher delivering the intervention. The researcher delivering the programme will review sessions, document adaptations and implement any necessary adaptations in subsequent group classes. These documented adaptations will inform ongoing refinement of the intervention, interpretation of feasibility outcomes, and future implementation.

Detailed intervention materials, including exercise and educational content, will be made available alongside the publication of the study findings, informed by the feasibility outcomes.

